### Sample size and power

The sample size for our trial is fixed by the primary hypothesis in the main SCC Trial, which estimated a total sample of 2184 mother–infant pairs from 104 clusters.^12^ We can find no reports of intracluster correlation coefficients (ICCs) for the women’s empowerment indicators we plan to use. Therefore, we estimate that the fixed trial sample size will provide at least 80% power to detect a 20% increase in women’s empowerment, assuming 30% of women are empowered and a high ICC of 0.2. Assuming a lower ICC of 0.05, we will have 90% power to detect a 13% increase in women’s empowerment.

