### Objectives and hypotheses

This study evaluates the impact of a combined nutrition counselling and an unconditional cash transfer RCT (SCC Trial), delivered on a mobile platform, on the level of empowerment of women in rural Bangladesh. This study will assess women’s experience of empowerment and disempowerment throughout the SCC trial.

The primary hypothesis is that in a community-based cluster RCT of a mobile phone-based nutrition BCC and unconditional cash transfer given to women in low-income families in rural Bangladesh, women’s empowerment will increase as measured by an increase in mean women’s empowerment scores (by an average percentage of 20) from the baseline to the end of the 24-month intervention, compared with women in the control arm.

The secondary hypotheses are that the mobile phone nutrition BCC and unconditional cash transfer compared to usual programmes will (1) increase control over income and economic resources, (2) improve input and decision-making power in nutrition and health care choices, and (3) decrease the acceptance and experience of IPV.

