### Allocation of clusters

Our study site has over 1100 villages, which would be adequate to cover the anticipated sample size. Each cluster encompasses two to four villages and consists of ~1000 households and ~4500 population. We will use a fixed randomisation scheme to assign treatments to eligible clusters, with a uniform allocation ratio of treatments, stratified by union. The sample size will consist of 104 clusters, total women (n=2840) allocated to two parallel groups (n=1420) with 20 mother–infant dyads per cluster. Each cluster consists of one to four adjacent villages with a minimum population of 600 households per cluster with 454 villages in our study area for clustering. A subsample of the households from a purposively selected subset of clusters will be chosen for qualitative data.

The intervention and control groups will receive similar maternal and child health and nutrition services from the government, and the critical difference will be the nutrition BCCs with cash transfers on a mobile platform received by women in the intervention arm. The study design will control for potential observed and unobserved confounding factors as there will be an adequate number of clusters randomly allocated to the treatment groups. The geographical separation of clusters will limit the contamination of the intervention arm. We will use STATA V17 software to generate the random allocation sequence. We are unable to mask the treatment arm due to the nature of the intervention.

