### Quantitative data analysis

Data analysis will be by intention to treat. The women’s empowerment composite index scores will be categorised as the percentage of women as empowered or disempowered. For each empowerment indicator, individuals are classified as adequate or inadequate based on Pro-WEAI predetermined thresholds. Women are considered empowered if four out of six indicators are adequate. We will also analyse impact of SCC intervention on individual indicators to assess increases or decreases in empowerment as not all indicators will respond or be impacted in the same way.

Analyses will be conducted at the mother–infant dyad level but will be adjusted for the cluster randomisation.^39^ Primary analyses will compare the prevalence of women’s empowerment at the end of the trial using Pearson’s χ^2^ tests and 95% CIs for the group difference, adjusted for clustering and generalised linear mixed models for non-continuous outcomes (eg, logistic mixed models for binary outcomes, for example, percentage of women’s empowerment). Models will include treatment group as a fixed effect, infants as a random effect to account for repeated measurements, and community cluster as a random effect to account for cluster effects. We will also assess if the women’s empowerment level at baseline, age, education, and presence or absence of a mother-in-law in the household modify the empowerment response to the intervention by testing for interactions between the intervention and these factors. STATA will be used for all analyses.

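### The power statement leaves the scale of its 20% and 13% increases unstated, and its 80% and 90% figures do not reproduce for the planned end-of-trial comparison

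*Protocol article*

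**What the plan says.** All statements are in the protocol article.

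- **Sample size and power.** The sample is set by the parent trial, "which estimated a total sample of 2184 mother–infant pairs from 104 clusters". From this the authors claim "at least 80% power to detect a 20% increase in women’s empowerment, assuming 30% of women are empowered and a high ICC of 0.2". The second claim is: "Assuming a lower ICC of 0.05, we will have 90% power to detect a 13% increase in women’s empowerment". No significance level is given, and neither increase is labelled relative or absolute.
- **Objectives and hypotheses.** The primary hypothesis is "an increase in mean women’s empowerment scores (by an average percentage of 20) from the baseline to the end of the 24-month intervention", compared with the control arm. It concerns mean scores, not a proportion, and again gives no scale for the 20.
- **Quantitative data analysis.** Women are classed as empowered or not, and "Primary analyses will compare the prevalence of women’s empowerment at the end of the trial", adjusted for clustering and with 95% confidence intervals.
- **Allocation of clusters.** "The sample size will consist of 104 clusters, total women (n=2840) allocated to two parallel groups (n=1420) with 20 mother–infant dyads per cluster", "with a uniform allocation ratio of treatments, stratified by union". These totals differ from the 2184 used for power, and 104 × 20 = 2080 matches neither.

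**The concern.** The sample was fixed by another trial, so this statement is the protocol's only account of what the empowerment comparison can detect. From 30%, a 20% increase means 36% if relative and 50% if in percentage points; a 13% increase means 33.9% or 43%. These are very different targets, and the stated power should match one of the two pairs. If it matches neither, a reader cannot judge what a null result would mean. On the relative scale, such a result could be taken as informative when the study had little chance of finding the effect. On the percentage-point scale, readers would think the study less sensitive than it is.

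**Working it through.** **Inputs**

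- 2184 women in 104 clusters, so 2184 / 104 = 21 per cluster (Sample size and power).
- Equal allocation, so 52 clusters and 1092 women per arm (Allocation of clusters).
- 30% empowered without the intervention; ICC 0.2 or 0.05 (Sample size and power).
- Comparison of two end-of-trial proportions, adjusted for clustering (Quantitative data analysis).
- Two-sided 5% level. This is my assumption, in line with the 95% intervals.

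**Formulas**

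- Design effect = 1 + (m − 1) × ICC
- Effective n per arm = 1092 / design effect
- SE = √[(p0(1 − p0) + p1(1 − p1)) / effective n]
- Power = Φ(|p1 − p0| / SE − 1.96)

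**Attempt to reproduce the stated figures**

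ICC 0.2: design effect 1 + 20 × 0.2 = 5.0; effective n = 1092 / 5 = 218.4 per arm.

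- Relative, 30% vs 36%: SE = √[(0.21 + 0.2304) / 218.4] = 0.0449; 0.06 / 0.0449 = 1.34; power = Φ(−0.62) = 27%.
- Points, 30% vs 50%: SE = √[(0.21 + 0.25) / 218.4] = 0.0459; 0.20 / 0.0459 = 4.36; power = Φ(2.40) = 99%.

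ICC 0.05: design effect 1 + 20 × 0.05 = 2.0; effective n = 1092 / 2 = 546 per arm.

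- Relative, 30% vs 33.9%: SE = √[(0.21 + 0.2241) / 546] = 0.0282; 0.039 / 0.0282 = 1.38; power = Φ(−0.58) = 28%.
- Points, 30% vs 43%: SE = √[(0.21 + 0.2451) / 546] = 0.0289; 0.13 / 0.0289 = 4.50; power = Φ(2.54) = 99%.

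| Claim | Stated | Relative | Percentage points |
|---|---|---|---|
| 20%, ICC 0.2 | at least 80% | 27% | 99% |
| 13%, ICC 0.05 | 90% | 28% | 99% |

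**What the design can detect**

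Solving the same formula for the difference gives 12.8 points at 80% power with ICC 0.2, and 9.3 points at 90% power with ICC 0.05. A 13-point difference (30% vs 43%) has 81% power at ICC 0.2.

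**Could a smaller ICC rescue the relative reading?**

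With no clustering at all (1092 independent women per arm), 30% vs 36% has 85% power, but 30% vs 33.9% has SE = 0.0199, ratio 1.96 and power of only 50%. So no ICC gives the stated 90% for a relative 13%.

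**Does the sample total matter?**

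With 104 clusters of 20 (2080 women) or 27.3 (2840 women), relative power is 26–27% at ICC 0.2 and 28–31% at ICC 0.05. Percentage-point power stays at 99% or above. The detectable differences are 12.5–12.8 points and 8.8–9.4 points.

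**Other variants (2184 women)**

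- Loss of 10–30%: percentage-point power 98–99%; relative 24–27%.
- Coefficient of variation of cluster size 0.7: percentage-point 95% and 98%; relative 20% and 23%.
- Formula based on the between-cluster coefficient of variation: percentage-point 92% and 98%; relative 23% and 26%.
- Two-sided 1%: percentage-point 96% and 97%.
- One-sided 5%: relative 38% and 40%.

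None of these end-of-trial variants gives roughly 80% and 90% together.

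**Change from baseline, in percentage points**

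If the two arms' changes are compared with zero correlation between baseline and endline, the variance is (3 × 0.21 + p1(1 − p1)) / effective n.

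- ICC 0.2, 30% to 50%: SE = √[(0.63 + 0.25) / 218.4] = 0.0635; ratio 3.15; power 88%.
- ICC 0.05, 30% to 43%: SE = √[(0.63 + 0.2451) / 546] = 0.0400; ratio 3.25; power 90%.

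With a correlation of 0.2 these rise to 94% and 95%.

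**The case against.** A reader might infer that the trial has only about a quarter of the power needed for its primary hypothesis, or that the figures are wrong however they are read. Neither follows from the documents.

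- On the percentage-point reading, 99% satisfies a claim of at least 80%, so the first sentence is then true. The second is wrong only in the conservative direction. This stands.
- The outcome is reported as a percentage of women, for which an increase of 20% is often loosely written to mean points. The percentage-point reading meets or exceeds both stated powers, while the relative reading comes near neither. The wording of the primary hypothesis does not settle the scale, because it concerns mean scores. This also stands, and it favours points.
- The change-from-baseline calculation comes close to the stated pair, and the hypothesis does speak of change from baseline. That may be where the figures came from. But the power section mentions neither the method nor a correlation, zero correlation is an unusual assumption for the same women measured twice, and the planned primary comparison is of end-of-trial prevalence. At best, then, the power was calculated for a different analysis from the one planned.
- Details such as the formula and significance level may sit in the full protocol or the parent-trial paper. That is fair, and their absence is not the finding. The finding is that the figures printed do not follow from the inputs printed beside them.

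**Conclusion.** The point holds as an unstated scale combined with figures that do not reproduce. Under the end-of-trial comparison, the 90% for 13% fails on both readings: about 99% in points, about 28% if relative. The 80% for 20% is true but uninformative in points (about 99%) and badly wrong if relative (about 27%). In points, the quoted effects exceed what the design can detect by about 7 points (20 against 12.8) and 4 points (13 against 9.3). A lack of power is not shown; it arises only if a relative increase was intended, which fits the printed numbers less well. These results assume a two-sided 5% level, 52 equal clusters per arm and no loss to follow-up. The variants above move the percentage-point power no lower than 92% and, at two-sided 5%, keep the relative power between 20% and 31%. The statement should be corrected because it is the only account of what the fixed sample can detect.

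**What to change.** 1. Reconcile 2184, 2840 and 104 × 20 = 2080 before restating power. The result barely changes, but the cluster size has to be stated once.
2. In the power section, give the control and intervention percentages, the significance level, cluster size and ICC, and replace both claims with figures that follow. With 21 women per cluster, for example: 80% power for about 13 percentage points (30% vs 43%) at ICC 0.2, and 90% power for about 9 points (30% vs 39%, or 9.3 points before rounding) at ICC 0.05, two-sided 5%.
3. If a relative 20% (30% vs 36%) was intended, report power of about 27% at ICC 0.2.
4. If a change-from-baseline calculation was used, say so, give the assumed correlation, and reconcile it with the end-of-trial comparison in the analysis section.
5. Align the target on mean scores in the primary hypothesis with the proportion empowered used for power and analysis. Simply adding percentage points to the hypothesis would not do this, because it would put the scale of a proportion on a mean score.

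The cost is wording only, with no change to enrolment. If a relative effect was meant, the stated power becomes much less favourable.

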### Data collection methods

The SCC Trial will collect key household data and nutrition indices, while this study collects data on women’s empowerment using the Pro-WEAI, whose focus is measuring agency for which there are limited, if any, standardised measures.^21^ We will include the Pro-WEAI Nutrition and Health Module and supplementary questions regarding IPV. The qualitative component will be tailored to context-specific issues and guided by formative research.

### Quantitative data

We will collect the women’s empowerment indicators in household surveys at the baseline and the endline of the 24 month study in the intervention and non-intervention arms. We will pretest all questions before the commencement of the study. We will use the validated short version of Marlowe-Crowne’s social desirability scale,^33^ which is based on a subset of 13 items from the original scale. We will calculate a social desirability score by adding up the number of socially desirable answers, out of the 13 questions. The potential range of the score will be from 0 to 13, and we will create three categories with a score of 0–4 graded as a low score, 5–9 as a medium score and 10–14 as a high score (online supplemental appendix table 3). The questionnaire assesses whether social desirability bias or the tendency of respondents to answer questions in a way viewed favourably by the research team has influenced the data collected. We will train the field researchers in detecting social desirability bias in qualitative data and limit bias by properly introducing the study to the respondents, building rapport and asking context-specific probing questions following the recent framework described by Bergen and Labonté.^34^ We will follow the process throughout the research.

### Qualitative data

The study uses qualitative analysis to elicit a local understanding of women’s empowerment and the linkages between the SCC Trial and women’s empowerment outcomes. We will generate qualitative data on women’s and men’s perceived and experienced change in empowerment through longitudinal qualitative semistructured in-depth interviews. We will also interview key family members as suggested by the women, for example, husband or mother-in-law.

We will explore the myriad of ways that women and men perceive and describe empowerment in their communities. A purposive sample will be interviewed approximately 2 months after the start of the intervention and at the endline of the SCC Trial. Due to the highly sensitive nature of the topics, a separate team of interviewers, from a different Upazila, will be trained to collect data on women’s empowerment and IPV. We will train the team in line with the ethical and safety procedures as per the WHO’s guidelines.^35^ The training will cover measures such as changing topics and asking a decoy nutrition question if anyone comes into the interview space and having details of referral and support services for women affected by or experiencing IPV.

#### Pro-WEAI

The Pro-WEAI measures the empowerment of women, agency and inclusion in the agriculture sector.^21^ It is a standardised, survey-based internationally validated index developed to adapt to project-specific contexts and has been piloted in Bangladesh.^17 21^ This study uses Kabeer’s conceptual framework of empowerment that focuses on the ability of individuals to make choices, ‘a process of change during which those who have been denied the ability to make choices acquire such an ability’.^36 37^ Agency or the ability of the individual to make considered choices is at the centre of the framework and revolves around inter-related dimensions of resources, agency and achievements. This framework underpins the Pro-WEAI.^21^ This study will collect data from women, across 12 indicators that are equally weighted (figure 3), with the addition of the Project-specific Nutrition and Health Module.

**Figure 3 F3:**
[figure not shown]
Pro-WEAI: 3 domains of empowerment and 12 indicators.^21^ WEAI, Project-Level Women’s Empowerment in Agriculture Index.

#### Intimate partner violence

The Pro-WEAI includes questions on a woman’s attitude to IPV. We will collect additional data about personal experience and behaviour-specific questions regarding IPV, as opposed to her perceptions thereof. We took these questions from the WHO Violence Against Women and Girls Survey (Bangladesh 2015).^32^ We will also ask questions relating to cyberviolence.^38^

### Health and nutrition

The Pro-WEAI offers the option of adding project-specific modules, and for this study, we will add the Nutrition and Health Module. This module asks questions about decision making about nutrition and health indices for women and children.

### Data collection and management

Intervention and evaluation staff will be separated from and will not know the trial hypothesis to minimise assessment bias. Android tablets will be used in the field to enable interactive data collection. During each evaluation interview, the data collectors will be guided and navigated by the software. As soon as the field staff complete each interview, they will upload the data to the server at International Centre for Diarrhoeal Disease Research (icddr, b). The data will be retained on the tablet and copied/merged with files at icddr, b, with android tabs being synchronised with the server daily. We will systematically scrutinise the captured data and address any discrepancies as they occur. Qualitative narrative data will be captured in digital audio recorders and stored in the server from where we will check for quality and improvement for future interviews.

### Quantitative data analysis

Data analysis will be by intention to treat. The women’s empowerment composite index scores will be categorised as the percentage of women as empowered or disempowered. For each empowerment indicator, individuals are classified as adequate or inadequate based on Pro-WEAI predetermined thresholds. Women are considered empowered if four out of six indicators are adequate. We will also analyse impact of SCC intervention on individual indicators to assess increases or decreases in empowerment as not all indicators will respond or be impacted in the same way.

Analyses will be conducted at the mother–infant dyad level but will be adjusted for the cluster randomisation.^39^ Primary analyses will compare the prevalence of women’s empowerment at the end of the trial using Pearson’s χ^2^ tests and 95% CIs for the group difference, adjusted for clustering and generalised linear mixed models for non-continuous outcomes (eg, logistic mixed models for binary outcomes, for example, percentage of women’s empowerment). Models will include treatment group as a fixed effect, infants as a random effect to account for repeated measurements, and community cluster as a random effect to account for cluster effects. We will also assess if the women’s empowerment level at baseline, age, education, and presence or absence of a mother-in-law in the household modify the empowerment response to the intervention by testing for interactions between the intervention and these factors. STATA will be used for all analyses.

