### Study outcomes

The primary study outcome will be the difference in women’s empowerment scores in the intervention arm as compared with the control arm of the SCC Trial. Secondary study outcomes will include (1) control over income and economic resources, (2) input and decision-making power in nutrition and healthcare choices, and (3) experience and attitude towards IPV.

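### The primary analysis cuts the six-indicator empowerment count at four of six, although the hypothesis and outcome are on scores, so the primary test ignores change that does not cross the cut

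*Protocol article*

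**What the plan says.** The article describes the primary quantity on two scales.

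- **Objectives and hypotheses:** empowerment will rise "as measured by an increase in mean women’s empowerment scores (by an average percentage of 20") from baseline to the end of the intervention, relative to control.
- **Study outcomes:** "The primary study outcome will be the difference in women’s empowerment scores in the intervention arm" compared with control.
- **Quantitative data analysis:** each indicator is first classed as adequate or inadequate at Pro-WEAI thresholds. Then "The women’s empowerment composite index scores will be categorised as the percentage of women as empowered or disempowered", with the rule that "Women are considered empowered if four out of six indicators are adequate". The test follows the cut: "Primary analyses will compare the prevalence of women’s empowerment at the end of the trial".
- **Sample size and power:** the calculation is for the proportion, "assuming 30% of women are empowered and a high ICC of 0.2".

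The analysis section also plans a separate look at each indicator, because "not all indicators will respond or be impacted in the same way".

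**The concern.** Six adequate/inadequate indicators give a count from 0 to 6. The primary analysis keeps only whether that count reaches four. A woman who moves from 0 to 3, or from 4 to 6, contributes nothing to the primary comparison, and neither does a fall from 3 to 0. With 30% assumed empowered, 70% of women are assumed to be below the cut.

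The hypothesis asks whether the average level of empowerment rises. A percentage above a cut answers a narrower question, and the two can disagree when gains fall mainly well below or above the cut. The sample size is fixed by the stunting trial, so the scale of the primary test is one of the few things this sub-study can still change to use its data better.

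**Working it through.** **Inputs from the article.** 2184 women in 104 clusters with equal allocation, so 52 clusters and 1092 women per arm, 21 per cluster. 30% empowered in control. ICC 0.2 or 0.05 for the binary outcome. Increases of 20% (at least 80% power) and 13% (90% power). The article does not say whether these increases are absolute or relative.

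**Assumptions, not in the article.** Two-sided 5% level. Latent correlation between indicators of 0.3 to 0.5. The ICC of the count is the one implied by the same cluster effect that produces the binary ICC.

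**Step 1: the article's own power figures.** Effective n per arm = 1092 / (1 + 20 × ICC):

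- ICC 0.2: 1092 / 5 = 218.4
- ICC 0.05: 1092 / 2 = 546

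Power = Φ{[d − 1.96 √(2p̄(1−p̄)/n)] / √[(p₁(1−p₁) + p₂(1−p₂))/n]}, with d = p₂ − p₁ and p̄ the mean of the two proportions.

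| Reading | ICC 0.2 | ICC 0.05 |
|---|---|---|
| Percentage points | 30 to 50%: 99.1% | 30 to 43%: 99.4% |
| Relative increase | 30 to 36%: 26.5% | 30 to 33.9%: 28.1% |

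Neither reading gives the stated 90%. The stated 80% is met only as a loose lower bound, under the percentage-point reading. The difference detectable from 30% is 12.9 points (80% power, ICC 0.2) or 9.4 points (90% power, ICC 0.05). Using 2840 women instead hardly matters: 99.3% and 99.7% as percentage points, 27.3% and 31.0% as relative increases.

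**Step 2: power of the count when the binary test has 80%.** Six latent-normal indicators share a cluster component and a woman component. A common threshold is set so that 30% of control women have four or more adequate. The cluster component is set to give the binary ICC. The shift is applied to two, three, four or all six indicators and sized so that the binary test has 80% power. Power for the mean count then comes from the variance of cluster means (52 per arm, t with 102 df). The implied ICC of the count is about 0.08 (binary 0.05) or 0.29 to 0.30 (binary 0.2), and its SD is about 1.7 to 1.95.

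| Correlation | Binary ICC | 2 respond | 3 respond | 4 respond | 6 respond |
|---|---|---|---|---|---|
| 0.3 | 0.05 | 92.1% | 89.4% | 88.3% | 87.8% |
| 0.3 | 0.2 | 90.9% | 86.7% | 84.7% | 84.1% |
| 0.5 | 0.05 | 92.8% | 89.0% | 87.1% | 86.0% |
| 0.5 | 0.2 | 95.4% | 88.0% | 84.6% | 83.1% |

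Subtracting 80, the gain is 3.1 to 8.3 points with four or six responding and 6.7 to 15.4 with two or three. Integrating the same model numerically moves single cells by up to about 1.5 points. The ranges should therefore be read as about 3 to 9 and about 7 to 16. A cruder calculation with a constant design effect gives 3 to 12 points overall and puts three responders close to the four-to-six range.

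**Hand check of one cell** (correlation 0.3, binary ICC 0.05, all six respond). Count mean 2.56, SD 1.67, ICC 0.078. Design effect 1 + 20 × 0.078 = 2.56; effective n = 1092 / 2.56 ≈ 427; SE = 1.67 × √(2/427) ≈ 0.114. An 8-point rise in the percentage empowered (binary power 79.4%) goes with a rise of about 14% in the mean, 0.14 × 2.56 ≈ 0.36. Then Φ(0.36/0.114 − 1.96) ≈ 88%, or 86.4% with the unrounded rise.

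**Step 3: the article's stated effects.** As percentage points, the binary test is already near 99% and the count gains 0.3 to 0.9 points. As relative increases, the gain is about 1 to 8 points from a base near 27%.

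**The case against.** A reader might infer that the cut costs 5 to 15 points of power in most plausible scenarios. The document does not support this. It gives no score distribution, no correlation between indicators and no ICC for the count. The larger gains also need effects smaller than the percentage-point reading and only two or three responding indicators. The article selects the six indicators as those likely to be affected, and its theory of change links the intervention to all of them. Its remark that "not all indicators will respond or be impacted in the same way" means unequal response, not that several indicators show none. The four-to-six range is thus the closer match to the plan.

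A reader might also infer that the trial cannot see change below or above the cut. It can: each indicator is analysed, and income control, health and nutrition decisions and IPV are secondary outcomes. Several separate comparisons do not, however, replace one primary test of the overall level.

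Nor can the cut be called unjustified. The article gives no reason for four of six, but it refers to a supplementary table and an index source that are not shown.

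Finally, the mismatch could be closed by rewriting the hypothesis to match the percentage. That would make the document consistent but leave the lost information where it is. These points reduce the size of the concern. None shows that the primary test captures change on one side of the cut.

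**Conclusion.** The point holds, with a modest and conditional size. From the document alone, the primary analysis is on a percentage above a cut while the hypothesis and outcome are on scores, and change that does not cross the cut cannot move the primary result. The power cost ranges from under 1 point (stated effects as percentage points), through about 3 to 9 points (binary power 80%, four to six indicators responding), to about 7 to 16 (two or three responding). These figures rest on the assumed latent correlation of 0.3 to 0.5, the two-sided 5% level and the implied ICC of the count. The case for change rests first on agreement with the stated hypothesis and only second on power. The change should be made, but the trial does not depend on it.

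**What to change.** - **Quantitative data analysis:** make the primary test the between-arm difference at endline in the number of adequate indicators (0 to 6), in a linear or ordinal mixed model with the same cluster random effect. This matches the Objectives and hypotheses and Study outcomes sections.
- **Secondary result:** keep the percentage of women with four or more adequate indicators, with its cluster-adjusted difference and 95% CI.
- **Sample size and power:** restate the calculation for the mean count. Take its SD and ICC from pilot or baseline data, or label them as assumptions, and show power over a range. The SD of about 1.7 to 1.95 and the ICC of about 0.08 or 0.29 to 0.30 used here come from a model and are only starting values.

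The cost is revised wording and a new power statement, with no new data, visits or participants. The primary estimand changes from a percentage to a mean number of indicators, which is less direct to communicate, but the percentage is still reported.
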